### Intervention

Participants will undergo a standardized brain MRI protocol during hospitalization within 7 days of randomization into SATURN and again within 30 days of the 24-month end-of-study period. Subjects who already undergo a baseline MRI as part of institutional practice are not required to undergo a repeat baseline study-specific MRI to participate in SATURN-MRI, provided that the MRI complies with the study imaging protocol (Table 1).

**Table 1 Tab1:** SPIRIT figure

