### Study outcomes

The primary outcome is new CMBs and/or sulci with cSS on T2*-weighted (GRE or SWI) images at end-study compared to baseline. Additional outcomes include the count of new CMBs, progression of WMH, and incidence of covert new non-lacunar infarcts between baseline and end-study MRIs. Clinical outcomes of (i) recurrent ICH, (ii) MACCE, (iii) cognitive decline (telephone T-Montreal Cognitive Assessment T-MoCA; https://mocacognition.com/), and (iv) poor functional outcome (modified Rankin Scale (mRS) 4–6) [16, 17] will also be assessed to determine if their relationship with statin use is modified by the presence and burden of CMBs and cSS on baseline MRI. The details on how functional and cognitive outcomes are assessed and collected are described elsewhere [14].

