### Statistical considerations

#### Sample size calculations

The target sample size is 894, based on the following observations/assumptions. We previously reported that 57% of statin-treated patients admitted with acute lobar ICH had CMBs on MRI [6]. Although the estimated incidence rate of new CMBs per year in patients with lobar ICH on/off statins is unknown, the annual incidence rate in mixed stroke cohorts varies from 3 to 7% per year (average ~ 5% per year) [18–21]. In a cohort of 118 patients with probable CAA, 8.5% showed new CMBs without cSS progression, 18.6% showed cSS progression without new CMBs, and 9.3% showed new CMBs and cSS progression, for a total of 36.4% with progression of either CMBs and/or cSS over the 2.2 years of follow-up, or approximately 19% per year [18]. These data likely overestimate the incidence rate expected in SATURN-MRI because approximately 33% of SATURN patients are expected to have probable CAA, and another 40% possible CAA. Therefore, we opted to select a more conservative new CMB and/or cSS rate of 6% per year, for a total of 12% over 24 months in patients discontinuing statins. We postulated that statin therapy will increase the risk of new CMB and/or cSS at a rate that is similar to that reported for ICH in the SPARCL trial (HR 1.68, or absolute increase of 8% over 24 months). Based on these assumptions, a two-group comparison of independent proportions with 652 subjects will yield 80% power to detect an absolute increase of 8 percentage points associated with the continuation of statin therapy in SATURN. This sample size was further inflated to account for loss-to-follow-up (LTFU), withdrawal-of-consent, and death during the 2-year follow-up period of approximately 15%, as observed in other MRI sub-studies, such as NAVIGATE-ESUS [22] and PURE [23].

The sample size calculation assumes 1:1 statin continuation:discontinuation among subjects enrolled in the ancillary SATURN-MRI study, but this balance is not guaranteed. However, the power is maintained above 75% for allocation ratios in the interval between 0.6 (discontinuation arm 62.5% of the total sample) and 2.5 (discontinuation arm 28.6% of the total sample).

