#### Analyses related to the secondary aims

In order to explore whether the presence and burden (number) of CMBs on baseline MRI can be used as an imaging marker to stratify the risk/benefit of statin therapy, a proportional hazards model will be used to relate the time to symptomatic ICH recurrence to treatment assignment, the presence and burden of CMBs/cSS, and the corresponding interaction. The interaction term will be used to evaluate the heterogeneity of the treatment effect according to presence/burden, and the corresponding treatment effects and 95% confidence intervals will be constructed. The effects of statin continuation on the incidence of new ischemic MRI markers (WMH and covert infarcts) on end-study MRI will be evaluated via logistic regression model relating the presence of new markers to treatment assignment. Heterogeneity of the treatment effect across racial/ethnic subgroups will be explored by extending the proportional hazards model to include main effects for sex and racial/ethnic subgroups and their corresponding interactions with treatment and presence/number of new lesions.

The association between the incidence of new MRI markers on end-study MRI and deterioration of cognitive function, quantified by T-MoCA, and functional outcome, quantified by mRS, will be evaluated. As in the parent trial, the T-MoCA will be analyzed by considering cognitive decline (reduction of at least two points from the highest score to any subsequent assessment), as well as normal cognition (T-MoCA ≥ 20); the mRS will be dichotomized (0–3 vs 4–6). A generalized linear mixed effects model will be constructed for each outcome independently in order to relate outcome to treatment, time, and presence of new lesions; in addition to the adjustments for randomization covariates specified above, the models will include an indicator for baseline cognitive decline/dementia derived from the subject’s medical history.

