### Lost-to-follow-up and missing data

If a participant in the ancillary MRI study has an ischemic stroke or recurrent ICH before the end of the 2-year follow-up period and a clinical MRI is obtained for stroke assessment at one of the participating sites, this MRI may serve as the end-of-study MRI if it complies with the study imaging protocol and the subject is unable to return for the 24-month follow-up MRI. If the clinical MRI indicates the presence of new markers, this indicator will be carried forward to the end-of-study timepoint. The data will be considered missing if the MRI does not show new markers and is performed more than 3 months prior to the participant’s anticipated end-of-study visit. Missing outcome data related to the incidence of MRI markers will be handled in the analysis via multiple imputation.

Multiple imputation is generally considered the least biased imputation method, since it incorporates uncertainty associated with the imputed value into the analysis. Briefly, logistic regression is used to derive a distribution for the primary outcome, using the primary analysis covariates (treatment, statin dose and indication, current use or intent-to-use oral anticoagulants and/or antiplatelets post-ICH, and severity of enrolling ICH) plus additional clinically relevant baseline variables. A random sample from the resulting distribution is used to impute values. Multiple sample data sets with complete primary outcome data are generated; each imputed data set will be analyzed according to the specified primary analysis, and the results from the multiple imputed data sets are combined to obtain a single set of parameter estimates. The multiple imputation method assumes missing at random (MAR) which means that the probability of missing outcome data can depend on the observed values of the individual but not on the missing values of the individual.

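### The secondary mRS model counts death as a poor outcome but conditions on an end-study MRI finding that most participants who die will lack, and no rule says how deaths enter it

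*Protocol article*

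**What the plan says.** All references are to the protocol article.

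- **Outcome.** Study outcomes lists "poor functional outcome (modified Rankin Scale (mRS) 4–6", and Analyses related to the secondary aims repeats the split: "the mRS will be dichotomized (0–3 vs 4–6". Category 6 of this scale is death, so a death is an event.
- **Predictor.** The same section introduces the analysis as "The association between the incidence of new MRI markers on end-study MRI and deterioration of cognitive function" and functional outcome, then specifies a generalized linear mixed model for each outcome to "relate outcome to treatment, time, and presence of new lesions".
- **Timing of the predictor.** Under Intervention, the follow-up scan is done "again within 30 days of the 24-month end-of-study period".
- **Exception.** Under Lost-to-follow-up and missing data, if a participant has an ischemic stroke or recurrent ICH, has a clinical MRI and cannot return, "this MRI may serve as the end-of-study MRI if it complies with the study imaging protocol". New markers on that scan are carried forward. A scan without new markers counts as missing if it was done more than 3 months before the expected final visit.
- **Missing lesion status.** The same section states: "Missing outcome data related to the incidence of MRI markers will be handled in the analysis via multiple imputation". The variables it lists are treatment, the randomisation covariates and further baseline variables. Follow-up mRS, T-MoCA and vital status are not listed.
- **Deaths expected.** Sample size calculations allows for loss to follow-up, "withdrawal-of-consent, and death during the 2-year follow-up period of approximately 15" percent. No separate death rate is given.

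**The concern.** The outcome and the predictor are defined on different sets of people. The outcome is known for everyone who dies. The predictor is observed only for those scanned near 24 months, plus a few with a substituted clinical scan. Three treatments of deaths are possible under the text, and each departs from what the model is said to estimate:

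1. **Impute their lesion status.** A death then enters as a certain poor outcome with a lesion status drawn without using that outcome. It is also a 24-month finding for someone not alive at 24 months.
2. **Drop them.** The outcome labelled 4–6 becomes, in effect, 4–5.
3. **Keep only those with a substituted scan.** Early positive scans stay and early negative ones become missing, so the deaths that remain are selected toward new lesions.

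At stake is the third secondary objective, which links statin assignment, accrual of markers and functional outcome, and which the Summary and conclusions section relies on when it speaks of marker validation and functional decline.

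**Working it through.** **The plan's own figures.** The article gives no figure for the mRS model. Its only size calculation is for the primary outcome: 12% versus 20% with new lesions, 652 evaluable, 80% power. At two-sided 5% (assumed, as alpha is not stated) the usual formula gives 329 per arm, 658 in total, within 1% of 652. So 12% and 20% can be taken as the planning rates.

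**Inputs**
- Lesion prevalence L = (12% + 20%)/2 = 16%, under the article's 1:1 assumption.
- Poor mRS in survivors without new lesions p0 = 20%: assumed.
- Survivor odds ratio 2.0: assumed. Odds without lesions 0.20/0.80 = 0.25; with lesions 0.50, so p1 = 1/3.
- Share of survivors without a scan k = 5%, 10%, 15%: assumed. The last equals the article's whole allowance, which also covers deaths, so on that allowance it is the upper end.

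**A. Survivors only: imputing lesion status without mRS**

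Imputed status is unrelated to mRS, so those participants carry the overall risk into both groups:

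m = 0.16 × 1/3 + 0.84 × 0.20 = 0.2213

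Risk with lesions = (1 − k)/3 + k·m; risk without = (1 − k) × 0.20 + k·m.

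At k = 15%: 0.2833 + 0.0332 = 0.3165 and 0.1700 + 0.0332 = 0.2032. Odds are 0.4631 and 0.2550.

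| Imputed share k | Odds ratio (true 2.0) |
|---|---|
| 5% | 1.94 |
| 10% | 1.88 |
| 15% | 1.82 |

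The estimand is the same throughout, so this is imputation bias alone.

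**B. Deaths imputed at the average lesion rate**

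Take 894 participants and 10% deaths (assumed): 89.4 deaths and 804.6 survivors. Survivor cells are 42.9 poor and 85.8 not poor with lesions, and 135.2 poor and 540.7 not poor without. If a share q of deaths truly have new lesions, the death-inclusive odds ratio is

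(42.9 + 89.4q) × 540.7 / [85.8 × (135.2 + 89.4(1 − q))].

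| True lesion share among deaths q | Odds ratio with true status | After imputing at 16% |
|---|---|---|
| 16% | 1.71 | 1.71 |
| 25% | 2.03 | 1.71 |
| 40% | 2.62 | 1.71 |

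The bias is zero if deaths have average lesion prevalence and grows with any link between lesions and death. Deaths would make up 89.4/(89.4 + 42.9 + 135.2) = 33% of all poor outcomes here.

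**C. Only carried-forward positive scans kept among deaths**

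If 10% of deaths have such a scan and the other deaths are dropped, only the poor-with-lesions cell grows. At 10% deaths: (42.9 + 8.9) × 540.7/(85.8 × 135.2) = 2.42. At 5% and 15% deaths the result is 2.20 and 2.66. The survivor value is 2.00. Against the true values in table B, 2.42 is too high for q = 16% or 25% and too low for q = 40%, so inflation is possible but not certain.

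**D. All deaths dropped**

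The odds ratio is 2.00, the survivor value, but for mRS 4–5 versus 0–3.

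**The case against.** The strongest reply is that this is silence, not error. The missing-data section describes imputation for the primary outcome, with each completed data set run through the primary analysis. In the mRS model lesion status is a predictor, and nothing states that imputed status feeds it. The handling of deaths in a secondary model could sit in the analysis plan, which is not shown. Much of this stands: a reader might infer that every death receives an imputed lesion status, and the article does not say so.

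Two other tempting readings also fail. A reader might say that lesion status cannot exist for anyone who died, but the substituted clinical MRI provides it for some. A reader might also take the survivor odds ratio of 2.0, add deaths at the average lesion rate, obtain 1.83, 1.76 or 1.68 at 5%, 8% or 12% deaths, and call the fall imputation bias. The same figures arise if every lesion status is known exactly and death is unrelated to lesions (the first row of table B shows this at 10%). They compare a survivor odds ratio with a death-inclusive one.

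It is also fair that the plan is a mixed model with a time term, so participants who die later may contribute earlier mRS values, which a single-time table ignores. Restricting to survivors, moreover, conditions on a post-randomisation event.

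What remains is that the article itself fixes the outcome, the predictor's timing, the one-sided carry-forward rule and the imputation variables. No choice for deaths within those settings gives the association as described.

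**Conclusion.** The point holds as a recommended change to a secondary analysis. The mRS model pairs a death-inclusive outcome with a predictor that most participants who die before 24 months will lack, and the article does not settle how they are handled. The direction of the error depends on that choice: toward the null if the listed imputation model is used, a changed outcome if deaths are dropped, and possible inflation if only carried-forward positive scans are kept.

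The size is illustrative. With 20% poor mRS without lesions and 16% lesion prevalence, imputing without mRS for 15% of survivors moves an odds ratio of 2.0 to about 1.82, and to 1.94 for 5%. The 20%, the odds ratio and all death rates are assumptions. The primary treatment comparison does not use this model and is unaffected. Effect modification by baseline markers is not touched either, since that predictor is read on the baseline MRI.

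**What to change.** In Analyses related to the secondary aims, and in the missing-data section where it bears on them:

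1. Keep mRS 4–6, including death, for the randomised comparison, without the end-study lesion term.
2. Estimate the lesion–function association in participants alive at 24 months, as mRS 4–5 versus 0–3, and state that it is conditional on survival. Do not impute lesion status after death for this analysis.
3. When imputing lesion status for survivors without a scan, include 24-month mRS, and T-MoCA for the cognitive models.
4. Tabulate deaths by arm beside the association.

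This changes analysis wording only; no extra data or visits are needed. The cost is fewer events and an association that applies to survivors and can be affected by selection through survival.

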#### Secondary objectives

To assess whether the presence and burden of CMBs and cSS on baseline MRI modifies the effects of statin on the risk of recurrent symptomatic ICH and can potentially be used as an imaging marker to stratify the benefit-risk of statin therapy in patients with lobar ICH. We also aim to examine the modifying effects of these markers on the risk of MACCE.To evaluate the effects of statin continuation vs. discontinuation on the incidence of new ischemic MRI markers (white matter hyperintensities (WMH) and covert infarcts) on end-study MRI.To evaluate interactions between statin continuation vs. discontinuation, accrual of MRI markers of CSVD, and functional and cognitive outcomes at the end of the study at 24 months.

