### Randomization

Patients will be randomized into the SATURN trial using the following stratification variables: clinical site, statin dose and indication (primary vs. secondary prevention), current use or intent-to-use oral anticoagulants and/or antiplatelets in the long-term post-ICH, and severity of ICH upon presentation as assessed by baseline ICH volume. There is no additional randomization procedure for the SATURN-MRI ancillary study.

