### Data analyses

The primary analysis will be conducted according to the intention-to-treat principle, meaning that all subjects are analyzed as a member of the treatment group to which they were randomly assigned in SATURN, even if the subject crosses over from one treatment arm to another. Secondary analyses will be conducted according to an on-assigned-treatment analysis. All models will be adjusted for the aforementioned randomization covariates as specified for SATURN (statin dose and indication, current use of or intent-to-use oral anticoagulants and/or antiplatelets post-ICH, and severity of enrolling ICH) [14].

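### The T-MoCA and mRS models for new lesions leave out baseline CMB, cSS and WMH burden, so the lesion coefficient can mix accrual with disease already present at entry

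*Protocol article*

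**What the plan says.** The third secondary objective in the Protocol article concerns statin assignment, "accrual of MRI markers of CSVD, and functional and cognitive outcomes at the end of the study at 24 months". The section on analyses related to the secondary aims turns this into an evaluation of "The association between the incidence of new MRI markers on end-study MRI and deterioration of cognitive function" and of functional outcome. A generalized linear mixed model is fitted for each outcome "in order to relate outcome to treatment, time, and presence of new lesions".

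The adjustment set is stated in two places:

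- Data analyses: "All models will be adjusted for the aforementioned randomization covariates as specified for SATURN". These are statin dose and indication, antithrombotic use or intent, and severity of the enrolling hemorrhage. Under Randomization, severity means "severity of ICH upon presentation as assessed by baseline ICH volume", which does not measure small vessel disease.
- Analyses related to the secondary aims: in addition, "the models will include an indicator for baseline cognitive decline/dementia derived from the subject’s medical history".

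There are three outcomes. Cognitive decline is a drop of at least two points from the patient's highest T-MoCA to any later assessment. The other two are levels: T-MoCA of 20 or more, and mRS 0–3 versus 4–6.

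Under Imaging analyses, the core lab grades CMB number and location, cSS extent and WMH (Fazekas and volume). Baseline CMB/cSS burden enters the hazards model for recurrent ICH, but not the T-MoCA and mRS lesion models.

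**The concern.** Randomization protects the comparison of arms. It does not protect the comparison of patients with and without new lesions, which is observational. A patient with advanced small vessel disease at entry is plausibly more likely to gain lesions and also more likely to have poor cognition or function at 24 months. None of the listed covariates measures that burden on imaging, and a yes/no history of cognitive decline is only a partial proxy. For the two level outcomes, impairment already present at entry counts as outcome.

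The lesion term could therefore reach significance when accrual itself adds nothing. This matters because the Introduction describes accumulating microvascular injury as contributing to cognitive and functional decline, and the Summary hopes the results will help to limit such decline later in life. A reader would naturally take a positive lesion coefficient as support for that view.

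**Working it through.** **Inputs from the article (Sample size calculations).** 652 evaluable subjects; about 33% with probable CAA and another 40% with possible CAA; in a probable-CAA cohort, new CMBs only 8.5%, cSS progression only 18.6%, both 9.3%, "for a total of 36.4% with progression of either CMBs and/or cSS over the 2.2 years of follow-up"; new CMBs in mixed stroke cohorts 3–7% per year, average about 5%; new-lesion risk over 24 months 12% off statins and 20% on statins.

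**Reproducing the plan's figures.** The alpha is not stated; two-sided 5% is assumed. With unpooled variance, n per arm = (1.96 + 0.84)² × (0.12×0.88 + 0.20×0.80) / 0.08² = 326 after rounding up, so 652 in total, as stated. The annual rate is 1 − (1 − 0.364)^(1/2.2) = 18.6%, matching the stated 19%.

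**How strongly does disease at entry predict new lesions?** The article allows two contrasts:

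- CMB only in both groups: (8.5 + 9.3) = 17.8% over 2.2 years, or 17.8 × 2/2.2 = 16.2% over 24 months, against 2 × 5% = 10%. Odds ratio (0.162/0.838)/(0.10/0.90) = 1.7.
- Composite against CMB only: 36.4% against 10%. Odds ratio (0.364/0.636)/(0.10/0.90) = 5.2. The endpoints differ, and the 36.4% covers 2.2 years rather than 2.

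The implied overall new-lesion rates are 0.33×16.2 + 0.67×10 = 12.0% and 0.33×36.4 + 0.67×10 = 18.7%. Both lie within the plan's 12–20%, so that range rules out neither contrast.

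**Assumptions not in the documents.** Poor-outcome risk 30% in the reference group; dementia history 15% with and 8% without baseline disease, with odds ratio 3 on the outcome; other randomization covariates unrelated to baseline burden; baseline disease a single yes/no factor; odds ratio of baseline disease on outcome varied from 1.5 to 3. The true lesion odds ratio is 1.0. A logistic model for a level outcome at 24 months stands in for the planned mixed model.

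**Rejection rate of the lesion term at nominal 5%, N = 652** (2,000 runs per cell for 36.4% vs 10%, 3,000 for 16.2% vs 10%):

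| New-lesion risk, probable CAA vs others | OR 1.5 | OR 2.0 | OR 2.5 | OR 3.0 |
|---|---|---|---|---|
| 16.2% vs 10%, planned covariates | 5.1% | 7.3% | 8.4% | 8.7% |
| 25% vs 10%, planned covariates | 7% | 13% | 19% | 25% |
| 36.4% vs 14%, planned covariates | 9% | 19% | 28% | 37% |
| 36.4% vs 10%, planned covariates | 11.0% | 23.6% | 40.8% | 52.2% |
| 36.4% vs 10%, baseline disease added | 5.0% | 4.9% | 5.0% | 4.0% |

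The spurious lesion odds ratio is 1.04–1.15 in the first row and 1.17–1.51 in the fourth. A repeat of the first row gave about 6%, 7% and 10% at odds ratios 1.5, 2 and 3.

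**A second design** fixed the overall new-lesion rate at 16% and the overall outcome risk at about 30%, and varied the odds ratio of burden on lesions (2–5) and on outcome (1.5–3). With 33% high burden, the rate was 6.6% (odds ratios 2 and 1.5), 12.8% (3 and 2), 21.9% (5 and 2) and 43.0% (5 and 3). With 57%, the stated baseline CMB prevalence, it was 6.0%, 11.2%, 16.3% and 29.4%. When only one of the two links was present, it stayed at about 5%. With burden in the model it was 4.5–5.6% throughout, with a lesion odds ratio of 0.99–1.01.

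**The case against.** The strongest reply has five parts.

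1. **The article's figures do not establish a strong link.** A reader might infer from 36.4% in probable CAA against 3–7% per year in mixed stroke that baseline disease strongly predicts new lesions, and hence that the error rate at least doubles. The documents do not support this. The first figure counts CMB and/or cSS, the second CMB only. On CMB alone the odds ratio is about 1.7 and the inflation is small. The 10% for the remaining patients is also borrowed from mixed stroke, although many of them are expected to have possible CAA. This part stands as to size. It does not remove the concern, because the planned hemorrhagic endpoint includes cSS, so CMB alone may understate the link.
2. **The plan speaks of association.** That is true, and no causal estimand is stated. But the objective concerns accrual, and without baseline burden the coefficient cannot separate accrual from disease at entry.
3. **Baseline CMB/cSS is planned elsewhere for these outcomes.** Study outcomes names it as a possible modifier of the statin effect on cognition and mRS. That is a different question. It is not carried into the lesion model, and WMH is not mentioned there.
4. **The decline outcome compares patients with their own highest score.** This partly removes differences in level, and this outcome was not simulated. That limit stands.
5. **An article condenses its plan.** This does not answer the point, because the covariates of these models are listed explicitly.

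**Conclusion.** The concern holds in a limited form. The stated adjustment set omits baseline CMB, cSS and WMH burden, so the lesion coefficient in the T-MoCA and mRS models is open to confounding by disease at entry. It can produce a spurious association; the documents do not show that it will.

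The size is uncertain. At baseline-disease odds ratios of 1.5 to 3, the false-positive rate is about 5–10% under the like-for-like CMB contrast and about 11–52% under the contrast of unlike endpoints. These rates rest on an assumed outcome odds ratio, an assumed outcome risk and a weak dementia proxy. They apply to a level outcome at 24 months, not to decline from the highest score or to the planned mixed model. The return to about 5% also assumes that the added terms capture baseline disease fully, as they do by construction in the simulation.

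A reader might infer that the statin effect or the primary result is biased. It is not: the omission bears on the new-lesion term, while the comparison of arms as randomized and the primary outcome do not depend on it. This is a worthwhile improvement to a secondary analysis.

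**What to change.** In the section on analyses related to the secondary aims, add three centrally read baseline measures to each T-MoCA and mRS lesion model:

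- CMB category (0, 1–2, 3–10, more than 10);
- cSS category (none, focal, disseminated);
- WMH (Fazekas score or volume).

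State that the new-lesion coefficient is interpreted as an association over and above baseline burden.

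Do not add the earliest T-MoCA or mRS score as a covariate where it is itself part of the outcome. It may be the highest score from which decline is measured, or one of the repeated outcomes in the mixed model.

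The cost is wording only, since the plan already provides for reading the baseline MRI. The statistical price is a few degrees of freedom and a slightly wider interval for the lesion term.
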